## 5. Ethics and Dissemination

This study received ethical approval from the Ethics Committee of the University of West Attica (protocol number 7889-08/02/2024). No further modifications are allowed, as the study has already been revised and approved in accordance with the recommendations of the Ethics and Conduct Committee of the University of West Attica. The trial will be conducted in accordance with the Declaration of Helsinki. The confidentiality of participants will be maintained throughout the study using coded identifiers and access to data will be limited to the research team.

## 6. Protocol Amendments

### 6.1. Confidentiality

During recruitment and before they participate in the study, a confidentiality statement and a brief version of the protocol will be signed by all participants as a consent form. This will also contain a signed statement ensuring confidentiality. A code number will be obtained at the time of randomization from each participant to ensure blinding and confidentiality. Participants’ personal information will be protected throughout the study, with no disclosure of identifiable data. Authorization to publish the study’s findings will be provided upon signing the written informed consent by the participant, the principal investigator, and two witnesses, which will specify that participants may withdraw at any time without penalty.

### 6.2. Access to Data

Access to the data will be allowed only to the principal investigator, the supervisor, and the statistician.

### 6.3. Support

Professionals and members of the Physiotherapy Department at the University of West Attica committee will have overall supervision of the study process and protocol. There will be monitoring of the participants and communication from the principal investigator for four weeks after the completion of the clinical trial to address any harm or problems.

## 7. Discussion

The purpose of this randomized controlled trial is to address a significant gap in the current literature concerning the impact of inspiratory muscle training (IMT) on diaphragm functionality and symptom management in individuals with gastroesophageal reflux disease (GERD).

To date, only a limited number of studies have investigated the effectiveness of IMT on maximum inspiratory pressure, symptom severity, and quality of life in patients with GERD. However, the heterogeneity of findings makes it difficult to draw certain conclusions. Strengthening the diaphragmatic component of the antireflux barrier may contribute to symptom reduction, given that the gastroesophageal junction is anatomically supported by diaphragmatic muscle fibers [45]. Previous studies have investigated the effects of IMT on the lower esophageal sphincter (LES) and the esophagogastric junction (EGJ) pressure, with contradicting findings. Specifically, Chaves et al. (2012) found no significant alterations in LES pressure after IMT, while Souza et al. (2013), in a pre–post clinical trial, reported enhancements in EGJ function and a reduction in transient LES relaxations, with a notable improvement in GERD-related symptoms [23,46]. Furthermore, a recent systematic review evaluating the effects of inspiratory muscle training on GERD-related outcomes reported significant improvements in maximum inspiratory pressure alongside a reduction in GERDQ scores [16]. Nevertheless, the authors have emphasized several methodological limitations, including the small number of available studies, lack of randomized controlled trials, absence of power calculations for sample size determination, heterogeneity of participant characteristics, and variability in outcome measures.

We should also bear in mind the introduction of a novel IMT technique supported by electronic devices, such as the K5 system. This technique presents further advantages in training over the threshold IMT. Thus, the study may further emphasize the clinical relevance of diaphragmatic strengthening, particularly considering the documented reduction in respiratory muscle strength among individuals with GERD [46]. Additionally, the combined use of objective clinical measurements and disease-specific questionnaires is expected to provide deeper insight into the interaction between GERD and respiratory function. The present study protocol adheres to established methodological standards, including appropriate randomization procedures, concealed allocation, examiner blinding, and justified sample size calculation, thereby enhancing the internal validity and reliability of the findings.

## 8. Conclusions

This randomized controlled trial is the first to examine the impact of inspiratory muscle training with a tapered flow resistive device on maximal inspiratory pressure, peak dynamic inspiratory pressure, symptom severity, and quality of life in individuals with gastroesophageal reflux disease. Although the findings are promising, additional high-quality studies are required to further substantiate the role of IMT as a non-pharmacological approach in the management of GERD.

## Figures and Tables

**Figure 1 mps-09-00032-f001:**
[figure not shown]
The design of the study is outlined in a flowchart prepared in line with the SPIRIT statement.

**Table 1 mps-09-00032-t001:** Standard protocol items: recommendations for interventional trials of this study (SPIRIT).

Study Procedures and Assessments	Enrollment (T-1)	Allocation (T0)	Baseline (T1)	Post-Intervention (T2)	Follow-Up (3 Months) (T3)

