### 3.4. Randomization and Blinding Procedures

The allocation concealment will be ensured through the randomization process. Sealed, opaque envelopes will be used, numbered consecutively by an Assistant Professor of the Laboratory of Advanced Physiotherapy, University of West Attica, who will not participate in any other process of the study. Participant assignment will be concealed from both participants and evaluators, while the principal investigator will be informed, in accordance with a single-blinding procedure.

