### 3.6. Outcome Measurements

The outcome assessments have been selected to capture both physiological changes in inspiratory muscle performance as well as clinically significant effects on the severity and frequency of GERD symptoms. A trained physiotherapist will perform: (a) MIP (Micro RPM), according to ERS statement [25,26], (b) S-index measurement (Powerbreathe K5) [27,28] and will administer the Reflux Disease Questionnaire [29,30,31] and Reflux-Qual Short Form Questionnaire [32,33]. All measurements will be performed in random order.

Respiratory function will be assessed with the measurement of FEV1/FVC% using the Spirolab iii spirometer (Medical International Research, Inc., Rome, Italy). This will be performed by a pulmonologist with adequate training.

All measurements will be performed at three pre-specified time points: at baseline (T1), immediately after completion of the 12-week intervention (T2), and at the six-month follow-up (T3) (Table 1).

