### 3.7. Interventions

An informative session on diaphragmatic breathing with simulated inspiratory muscle exercise after randomization will be given to participants of both groups. This will enhance the role of physiotherapy, specifically the development of a trusting relationship between therapist and participant, increasing their self-confidence [39]. The long-term goals of managing the underlying disease and the health belief model will determine the structure of the session [40].

Intervention group: Participants allocated to the intervention group will follow a 12-week inspiratory muscle training program consisting of three 15 min sessions per week in the morning or afternoon 2 h after breakfast or lunch [41]. Training will be performed using an electronic inspiratory muscle trainer that provides a tapered flow of load resistance, initially at 40% of each participant’s MIP performing 30 breaths per session with 1 set of 30 repetitions [24,42]. Resistance will be progressively increased on a weekly basis at a rate of 10% of the initial maximal inspiratory pressure measurement if patients at the end of the week experience difficulty 3–4 on the Borg scale [43]. Otherwise, the resistance will remain the same. Resistance will also be maintained if the participants present persistent reflux symptoms.

Control group: Participants assigned to the control group will perform sham inspiratory muscle training using the same device with a constant minimal resistance 7 cmH_2_O [23].

A training diary will be kept for all participants that will include all information on the progression of training, missed sessions (along with the reason) and monitoring of their symptoms and medication.

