**Allocation**					
Assignment to intervention/control groups		X			

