**Intervention**					
Study procedure implementation		X			
Inspiratory Muscle Training		X			

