**Outcome Assessments**					
Study assessments (overall)			X	X	X
Maximal Inspiratory Pressure (MIP)			X	X	X
Maximal Expiratory Pressure (MEP)			X	X	X
5-min measurement			X	X	X
Reflux Disease Questionnaire			X	X	X
Reflux Quality of Life—Short Form (RFSF)			X	X	X
Spirometry			X	X	X

Note: X indicates that the procedure or assessment was performed at the specified time point.

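### Table 1 lists allocation before baseline and no passage says otherwise, so the effort-dependent baseline MIP and S-index may be measured after randomisation

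*Protocol article*

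**What the plan says.** **Schedule (Table 1).** The columns run Enrollment (T-1), then "Allocation (T0", then Baseline (T1), Post-Intervention (T2) and Follow-Up (T3). The row "Assignment to intervention/control groups" is marked at T0 only. The row "Inspiratory Muscle Training" is also marked at T0 only. The row "Maximal Inspiratory Pressure (MIP" is first marked at T1, as are the questionnaires and spirometry. No row is labelled S-index; its timing comes from Section 3.6.

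**Time points (Section 3.6).** All measurements are taken "at baseline (T1), immediately after completion of the 12-week intervention (T2), and at the six-month follow-up (T3".

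**Training (Section 3.7).** The load is set "initially at 40% of each participant’s MIP", with weekly steps defined as a fraction of the initial MIP. The same section states: "An informative session on diaphragmatic breathing with simulated inspiratory muscle exercise after randomization will be given to participants of both groups".

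**Who knows and who measures.** Under Section 3.4, participants and evaluators are kept unaware of the assignment, while "the principal investigator will be informed". Section 3.6 gives MIP and S-index testing to a trained physiotherapist. Section 3.8 gives data collection before and after the intervention to the principal researcher. Section 7 claims examiner blinding.

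**Analysis (Section 4).** The primary analysis is a 2 × 3 repeated measures ANOVA of the interaction between group and time, with T1 as the first level of time.

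**The concern.** A baseline should be fixed before anyone can know the arm. Here it has two jobs: it is the reference for change in the primary interaction test, and the initial MIP determines the training load. MIP and S-index both depend on maximal effort, and Section 3.6.1 says that participants are encouraged to make that effort during the S-index manoeuvres. If the envelope is opened first, encouragement or scoring at T1 could differ by arm. A lower baseline in the training arm would then look like a gain from training. Testing before the envelope is opened removes that possibility at T1, whoever does the testing.

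The training row raises a second, separate matter: read literally, it puts the intervention before the measurement that sets its load.

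**Working it through.** **1. Does any passage put the T1 tests before randomisation?**

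- Table 1: allocation at T0, outcomes first at T1. This states the opposite order.
- Section 3.3: mentions spirometry and S-index measurement under recruitment. This hints at early testing but does not say that these are the T1 values or that they precede allocation.
- Section 3.5: mentions an initial assessment together with selection. Again a hint, with no order against allocation.
- Section 3.8: data are collected before the intervention. That is not the same as before randomisation.
- Section 3.7: the information session comes after randomisation; its place relative to T1 is not given.

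No visible passage overrides the table on this order.

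**2. Is the training mark at T0 consistent with the text?** Section 3.7 sets the load from measured MIP, and Table 1 first measures MIP at T1. Section 3.6 puts T2 immediately after the 12-week programme. Section 3.8 has data collected before the intervention. All three conflict with a single mark at T0.

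**3. How would a baseline shift travel?** Suppose there is no true effect, the training-arm baseline is under-measured by *b* SD, and T2 and T3 are unaffected.

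- Change from T1 (the contrast inside the interaction): spurious effect = *b*.
- Baseline-adjusted comparison with baseline-to-T2 correlation *r* and equal SDs: spurious effect = *r* × *b*. For example, 0.7 × 0.2 = 0.14 SD.

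Adjustment therefore reduces such a shift but does not remove it.

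**4. Illustration of scale.** The plan's own figure comes first. For d = 1.3, two-sided alpha 0.05 and 1:1 allocation, the noncentral t gives power 0.785 with 10 per arm and 0.826 with 11 per arm. The stated 22 in Section 3.5 is reproduced. The order of baseline and allocation does not enter that calculation.

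Now use 11 per arm (22 in Section 3.5) and 15 per arm (30 in the Abstract, assuming equal arms). The values of *b* and ρ are assumptions and come from no passage. The standardised shift in a change score is δ = *b* / √(2(1 − ρ)). The rejection rate is that of a two-sided t-test with noncentrality δ√(n/2) and 2n − 2 degrees of freedom.

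| *b* (SD) | ρ | δ | n = 11 per arm | n = 15 per arm |
|---|---|---|---|---|
| 0.2 | 0.5 | 0.20 | 7.3% | 8.3% |
| 0.2 | 0.7 | 0.26 | 8.9% | 10.5% |
| 0.2 | 0.8 | 0.32 | 10.9% | 13.3% |
| 0.5 | 0.5 | 0.50 | 20.1% | 26.2% |
| 0.5 | 0.7 | 0.65 | 30.2% | 40.0% |
| 0.5 | 0.8 | 0.79 | 42.3% | 55.2% |

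The nominal rate is 5%. These rates apply only if a shift of that size occurs at T1 and not at T2. A shift equal at all visits would cancel.

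**The case against.** The strongest reply is that this is an untidy table and no biased design has been shown. Several parts of that reply stand.

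- **A reader might infer that training starts before baseline.** The text does not support this. The load is set from MIP, T2 closes a 12-week programme, and data are collected before the intervention. The T0 mark is most likely a table error. It still has to be reconciled, and it weakens the table as evidence of the real sequence.
- **A reader might infer that the baseline definitely follows randomisation.** That is too certain. Sections 3.3 and 3.5 hint at earlier testing, and the flowchart in Figure 1 is not shown and may give the order.
- **A reader might infer that the post-randomisation session biases the comparison.** Both groups receive it. It could change what baseline means, but it would not by itself create a difference between arms.
- **A reader might infer that the assessor is unblinded.** The documents conflict. Section 3.4 keeps evaluators blind, Section 3.6 names a physiotherapist, and Section 7 claims examiner blinding. Section 3.8 points the other way, but only if the principal researcher is the principal investigator of Section 3.4. If participants and assessors are truly blind, a baseline taken after allocation but before training is not biased by arm.
- **Loss of participants between T0 and T1** is conjecture. No interval is stated, and both could fall on the same day.

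What the reply does not answer is the order itself. Allocation before baseline can be carried out as written, so it cannot be dismissed as an obvious slip in the way the training mark can. The conflict over who assesses is the reason not to rely on blinding alone.

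**Conclusion.** The point holds as a gap in protection. Table 1 states allocation before baseline, nothing visible corrects it, and the effort-dependent measures that anchor the primary interaction may therefore be taken once the arm is known to the principal investigator. Bias is possible; the documents do not demonstrate it. It requires that T1 does follow allocation and that someone aware of the arm influences the test. The size of any shift cannot be derived from the documents, and the rejection rates above illustrate assumed shifts only. The stated sample size is unaffected.

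The training mark at T0 is a separate internal contradiction with Sections 3.6, 3.7 and 3.8.

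**What to change.** - In Section 3.4 and Table 1, state that all T1 assessments (MIP, S-index, MEP, both questionnaires and spirometry) are completed before the next envelope is opened and before the information session.
- Place the Baseline column ahead of Allocation.
- Reconcile the training row with Sections 3.6 to 3.8. On the text's own account it spans T1 to T2.
- Check that Figure 1 shows the same order.

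The cost is one table and one or two sentences, with the same visits and staff. Section 5 says that the approved study may not be modified further, so the team should confirm that a clarification of sequence is admissible.

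This protects the baseline only. It does not settle who assesses T2 and T3, or whether that person is blind; Sections 3.4, 3.6 and 3.8 need to be reconciled on that separately.

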**Enrollment Procedures**					
Eligibility screening	X				
Informed consent obtained	X				
Collection of demographic data	X				
Inclusion of participants in study	X				
**Allocation**					
Assignment to intervention/control groups		X			
**Intervention**					
Study procedure implementation		X			
Inspiratory Muscle Training		X			
**Outcome Assessments**					
Study assessments (overall)			X	X	X
Maximal Inspiratory Pressure (MIP)			X	X	X
Maximal Expiratory Pressure (MEP)			X	X	X
5-min measurement			X	X	X
Reflux Disease Questionnaire			X	X	X
Reflux Quality of Life—Short Form (RFSF)			X	X	X
Spirometry			X	X	X

Note: X indicates that the procedure or assessment was performed at the specified time point.

## Data Availability

Data utilized and/or analyzed in this study can be obtained from the corresponding author upon reasonable request.
